### Who will take informed consent {26a}

Patient’s written consent will be obtained by the investigator prior to any study-specific procedures. Participation is voluntary, individuals may withdraw at any stage, and participation does not affect their treatment.

### Additional consent provisions for collections and use of participant data and biological specimens {26b}

We will take advantage of the existing “Immunology” research program declared by CHU Nantes to set up the “POLYCOR” biocollection. Biological samples will be collected and stored if the patient has signed the biocollection informed consent. In this informed consent form, it is noted that the samples may be used for other scientific research. This biocollection will be a biological and longitudinal follow-up of patients with diagnosis of COVID-19, to assess immune changes and host-virus interactions. Ethic authorization is already granted, and the preanalytical steps are already implemented and efficient.

### Interventions

#### Explanation for the choice of comparators {6b}

POLYCOR project has the aim to define the optimal XAV-19 dose to administrate to moderate COVID-19 pneumonia patients, and to evaluate its safety and efficacy.

French regulatory authorities (ANSM), thus, has given their scientific recommendation to conduct the first part of the study (phase 2a) as a first-in-human study, with sequential enrolment to check for safety.

Dose levels selected in the first-in-human assessment of XAV-19 are based on 3 datasets:
Clinical experience with LIS1 glyco-humanized swine IgG administration. LIS1 is an experimental lymphodepleting polyclonal swine antibody produced by the glyco-humanized GH-pAb platform of Xenothera Laboratory. It is currently in clinical development in kidney transplant patients in EU (EUDRACT 2019-000917-35). So far, the maximal dose that has been reached in the escalating dose arm and found acceptable by the DSMC (which recommended pursuing the trial at this dose) is five daily administrations of 8 mg/kg, i.e., a cumulated dose of 40 mg/kg. Therefore, in this first-in-human trial with XAV-19, we have proposed that the cumulative dose stays inferior to the maximal LIS1 dose administered.Published clinical experience gained with use of convalescent plasma (CP) containing anti-COVID-19 neutralizing antibodies, having evidenced improvement of clinical symptoms. First, critically ill patients with COVID-19 received two consecutive transfusions with 200 mL CP. CP had a SARS-CoV-2-specific antibody (IgG) binding titer greater than 1:1000 and a neutralization titer greater than 40 (end point dilution titers) [9]. In this experience, the ratio between binding and neutralization titers is therefore of 25-fold on the average. Second, Duan et al. treated 10 COVID-19 patients with one dose of 200 mL CP [21]. In this report, the average neutralizing titer calculated on 40 CP was > 1/160. Third, in a former clinical experience with 80 CP transfusions from SARS-convalescent patients in 2003, the average CP volume was 279 mL and the neutralizing titer was > 1/160 [22]. Thus, all together, estimating that transfusion of 200 mL CP corresponds to 25 mg/kg IgG (considering that plasma contains 10 mg/mL IgG and considering 80-kg patients), we can postulate that 25 mg/kg of an IgG preparation presenting a neutralizing titer of at least 1/40 presents a clinical interest. Binding and neutralization titers of glyco-humanized serum from which XAV-19 has been obtained were of approximately 1/100,000 and 1/4000 (in the ELISA neutralization assay). The neutralization titer in a cytopathogenic effect assay was of 1:1600. This neutralizing titer of XAV-19 is thus 40- to 100-fold higher (depending on the assay) as compared with COVID-19 CP presenting a clinical interest according to the literature, and 12.5-fold higher than recommended by the European Commission. It has been considered that the ratio of the neutralization titer in XAV-19 vs CP should be used in the dose selection. According to available data, a batch exhibiting a 40-fold ratio to CP might thus be used at a 40-fold inferior dose, which means that infusions of 0.6 mg/kg XAV-19 should result in similar effects in vivo as compared with 25 mg/kg CP. Recent guidance from the European Commission on use of CP revised desired neutralizing titers of CP and suggested that “neutralizing antibody titers should optimally be greater than 1:320, but lower thresholds might also be effective” (https://www.phc.org.ua/sites/default/files/users/user90/Guidance_plasma_covid19_en.pdf). Therefore, another, higher dose than 0.6 mg/kg XAV-19 might also be tested.PK/PD information obtained from ex vivo assessment of XAV-19. XAV-19 has been assessed in competition ELISA (inhibition of the COVID-19 spike protein binding to ACE-2 receptor) and tested in neutralizing activity assay against SARS-CoV-2 using classical plaque reduction test using Vero cells. Our data showed an IC_50_ (concentration for reaching 50% of maximal signal in the test) of approx. 2.5 μg/mL of the first batch of XAV-19 in these ELISA and neutralization assays [14]. Data from the cytopathogenic effect assay showed a complete inhibition of SARS-CoV-2 infectivity was reached around 15–25 μg/mL in the assay. Considering an average plasma volume of 38.5 mL/kg, infusions of 0.96 mg/kg of this batch of XAV-19 would be required to reach (at Cmax) 25 μg/mL plasma concentration (at Cmax). The volume of distribution of swine glyco-humanized IgG measured in primates (53 mL/kg) has a value close to that of the plasma suggesting that the XAV-19 IgGs will essentially circulate in the plasma. Considering also distribution and elimination half-life, estimated at 172 h in primates, we can select an initial dose 2-fold higher than this target, given on day 1 and day 5, so as to stay above a through level of 25 μg/mL over more than a week, a duration deemed appropriate to obtain a clinical response. The estimated dose to reach this target is 2 mg/Kg.

Based on these 3 datasets, the Pharmacologically Active Dose (PAD) Standard of Care SOC for Group 2 of phase 2a would be 2 mg/kg infused on day 1 and on day 5 for a batch of XAV-19 presenting the IC_50_ of 2.5 μg/mL in the ELISA Spike/ACE2 neutralization assay. It is meant to maintain trough levels of XAV-19 above 25 μg/mL over several days. This dosing is lower than the dose already administered in human in the previous clinical experience demonstrating safety with LIS1 (5 daily administrations of 8 mg/kg, thus a total of 40 mg/kg), thus lower than a dosing which might reach a dose limiting toxicity. In other words, this dosing (two administrations of 2 mg/kg) presents a 10-fold safety factor for the first administration of XAV-19, as compared with previous experience with glyco-humanized swine IgG. Based on this PAD, the first-in-human dose (group 1 of phase2a) can be set with a safety factor of four following the escalation guidelines of the European Commission. For the first-in-human dose, 0.5 mg/kg on day 1 and on day 5 is therefore proposed, i.e., a cumulated dose of 1 mg/kg. Thus, there is a 4-fold increment between group 1 and group 2 in the phase 2a.

The evaluation of safety and phamacokinetic parameters in both dosing groups will guide the choice for the dose to be used in the phase 2b study.

#### Interventions description {11a}

Phase 2a will enroll 16 subjects in one of the two dose-level groups: group 1 with dose level defined according to the neutralization titer of the XAV-19 batch (first estimation being 0.5 mg/kg) and group 2 as 4 times higher than group 1 (estimated 2.0 mg/kg). If a patient does not receive the full treatment or has not been followed for 8 days, then he/she will be replaced within the limit of 20 patients in total. Each subject will receive two infusions of XAV-19 or placebo separated by an interval of 4 days (administrations on day 1 and day 5).

More precisely, after enrollment of the first two patients in the low dose group (one patient treated and one patient placebo), data will be obtained after first (day 1) and second (day 5) infusions to collect any severe adverse events that might have occurred, especially in the first 48 h following each infusion.

DSMC will have to review immediately safety data of the first 2 patients (based on day 8 information) and provide advice on continuing enrolment of the 6 last patients of group 1 (low dose). DSMC statement, and sponsor decision with regard to study continuation will be immediately communicated to ANSM.

If there is no signal of severe intolerance by day 8 of enrollment of the first two patients, the rest of the group will be enrolled with the same process of review of tolerance.

When the final patient of group 1 has been enrolled, day 8 safety data of all 8 patients from this low-dose cohort will have to be reviewed by the DSMC to advise of starting high-dose group (group 2). DSMC statement and sponsor decision with regard to study continuation will be immediately communicated to ANSM.

At any time during the phase 2a study, if a serious adverse event occurs, this will be communicated to the DSMC and the sponsor and coordinating investigator will have the responsibility to decide whether DSMC must meet to advise on study conduct.

The same sequential XAV-19 administrations will apply for the second group dosed at 2 mg/kg, with safety steps and DSMC data review.

At the end of phase 2a and as requested by the French regulatory authorities (ANSM), an amendment will be made to the protocol to continue the study in phase 2b.

The phase 2b (DFD) will be a double-blinded, placebo-controlled randomized study to assess clinical benefit and safety of the phase 2a selected dose of XAV-19 in 352 hospitalized adults with COVID-19-associated moderate pneumonia. Patients will be randomized to either XAV-19 or placebo in a 1:1 ratio and will receive 2 consecutive doses 4 days apart (day 1 and day 5). Obviously, during this 2b study, the DSMC will regularly meet as defined in the DSMC charter.

During the phase 2b study, if the proportion of patients requiring invasive mechanical ventilation after inclusion increases to 30~50% (analyzed by incremental groups of 50 patients), the DSMC will be requested to review data without discontinuation of the study. If the proportion of patients requiring invasive mechanical ventilation after inclusion is greater than 50% of the patients included in the study (analyzed by incremental groups of 50 patients), inclusions will be temporarily stopped and DSMC will be requested to review data and decide on an early definitive discontinuation of the study.

The study diagram of these 2 studies are showed in Figs. 1 and 2.

**Fig. 1 Fig1:**
[figure not shown]
Diagram of phase 2a study. **a** Phase2a—group1. **b** Phase 2b—group 2

**Fig. 2 Fig2:**
[figure not shown]
Diagram of phase 2b study

The study schedule with all the visits is summarized in the flowchart showed in Fig. 3; all of these examinations apply to all patients from phase 2a and phase 2b, except for the specific blood samples specific to ancillary studies. In phase 2a, the blood collections apply for all patients. In the phase 2b, the following blood collections are part of ancillary studies as follows:

**Fig. 3 Fig3:**
[figure not shown]
Study schedule for phase2a and phase 2b

Ancillary study 1: 20 patients to evaluate the pharmacokinetic
▪ Lymphocyte sub-populations

Ancillary study 2: 30 patients from phase 2b to evaluate:
▪ Spike/ACE2 interaction neutralizing antibody sample▪ Lymphocyte sub-populations▪ Cytokines▪ Transcriptomic analyses▪ Single cell RNAseq on B cells▪ B-Tfh functional interaction

#### Criteria for discontinuing or modifying allocated interventions {11b}

In the event of early discontinuation of the study treatment, all efforts will be made by the investigator to invite the patient to undergo the end of visit. The primary reason for discontinuation must be recorded in the appropriate section of the e-CRF and all efforts made to complete and report the observations as thoroughly as possible.

If a patient fails to return for a scheduled visit/follow-up, attempts should be made to contact the patient to identify reason for not returning. Likewise, if a patient declares their wish to discontinue from the study, e.g., for personal reasons, all efforts should be made to establish that the cause is not due to an AE (bearing in mind the patient is not obliged to their reasons).

A definitive or temporary discontinuation of all or part of the study may be decided by ANSM, the Ethics Committee, the Sponsor after Data and Safety Monitoring Committee (DSMC) opinion*.*

In any case:
A written confirmation of this early discontinuation of the study shall be sent to the coordinating investigator of the study (specifying the reasons for the early discontinuation).All the patients included in the study shall be informed and should attend their early withdrawal visit.

Each early departure from the study should receive the usual medical follow-up.

#### Strategies to improve adherence to interventions {11c}

The studies will be realized in hospital; patient adherence is not applicable.

#### Relevant concomitant care permitted or prohibited during the trial {11d}

SOC for COVID-19 will be conducted per local practice and/or local/national guidelines at time of the study, which may include, not exclusively, antibiotics, antiviral treatment, corticosteroids, immune therapies not based on antibodies administration, and anticoagulants. Specifically, serotherapy for the current COVID-19 episode will not be permitted.

#### Provisions for post-trial care {30}

After the end of the study, each patient will receive the usual medical follow-up.

The sponsor takes out an insurance policy covering the financial consequences of its civil liability in compliance with the regulations.

### Outcomes {12}

The primary endpoints of the phase 2a study are the (a) pharmacokinetic measurement of the antibody titer of XAV-19 measurements of all treated patients and of all patients in the placebo group at day 8 (3 days after the last administration) and (b) tolerability and adverse events of XAV-19 between the two groups of treated patients and vs. placebo over 29 days, evaluated as:
Occurrence of all suspected XAV-19-related adverse effects and incidence of serious adverse eventsProportion of participants with treatment emergent adverse events leading to study drug discontinuationIncidence of major or bacterial or fungal infections during the hospital stayIncidence of hypersensitivity reactions and infusion reactions. To note AEs are registered up to day 60 and for infusion-related AEs, 48 h after.White cell count, hemoglobin, platelets, creatinine, ALT, AST, on day 1, day 3, day 5, day 8, day 15, and day 29SARS-CoV-2 viral load over time (day 1–day 29), as collected by nasopharyngeal swab samplesTime to RT-PCR virus negativity in nasopharyngeal swab samples

The secondary endpoints of the phase 2a are the:
Pharmacokinetic analysis: Antibody titer measurements at day 1 (pre-dose, post-dose), at day 3, day 5 (pre-dose, post-dose), day 8, day 15, and day 29.The antibody titer of XAV-19 measurements in group 1 treated patients and group 2 treated patients at day 15.Clinical aspects:Duration of supplemental oxygenTransfer to intensive care unit with need for invasive mechanical ventilation or high flow oxygenNormalization of fever ≥24 h: clinical assessment every day from day 1 to day 14. Evaluation to be performed between 8 and 12 am, day X evaluation will consider the higher value during day X-1 (8 am to 8 am)- Normal fever (≤ 37.8 °C tympanic or ≤ 36.6 °C axillary or ≤ 37.2 °C oral taken 4 h apart from antipyretic administration) each day and time to resolution of fever for at least 48 hBiomarkers: CRP, Ferritin (at days 1, 3, 5, 8, 15, and 29)Ordinal scale assessed at Day 15. The 7-point ordinal scale is an assessment of the clinical status at the first assessment on day 15. The scale is as follows:Not hospitalized, no limitations on activitiesNot hospitalized, limitations on activitiesHospitalized, not requiring supplemental oxygenHospitalized, requiring supplemental oxygenHospitalized, on non-invasive ventilation or high flow O_2_ devicesHospitalized, on invasive mechanical ventilation or ECMODeathHospital length of stay

The primary endpoint of the phase 2b is the time to weaning of supplemental oxygen.

If patient is still on oxygen at day 15 or if the patient is weaned but put back on oxygen, then the delay will be censored at 15 days.

The secondary endpoints are the:

National Early Warning Score (NEWS2) at day 15 and difference in NEWS2 between day 1 and day 15Clinical status using the 7-point ordinal scale assessed at day 3, day 5, day 8, day 11, day 15, and day 29Time to improvement of one category from admission using the 7-point ordinal scaleTime to first fever normalization (criteria for normalization: temperature < 36.6 °C armpit, < 37.2 °C oral, < 37.8 °C rectal or tympanic)Duration of oxygen therapy over 29 daysComparison of oxygen requirement between the two groups over 29 daysTime to weaning in supplemental oxygen and proportion without O2 requirement at day 15, according to baseline (day 1) oxygen requirement (≤ 4 L/min or 4 L/min)Incidence and duration of non-invasive ventilation or high flow oxygen devices, of invasive mechanical ventilation during the studyHospital length of stayAll-cause mortality at Day 29Safety of XAV-19 evaluated as:Occurrence of all suspected XAV-19-related adverse effects or incidence of serious adverse eventsProportion of participants with treatment emergent adverse events leading to study drug discontinuationIncidence of major or opportunistic bacterial or fungal infectionsIncidence of hypersensitivity reactions and infusion reactionsWhite cell count, hemoglobin, platelets, creatinine, ALT, AST, on day 1, day 3, day 5, day 8, day 11, day 15, and day 29SARS-CoV-2 viral load over time (day 1–day 29), as collected by nasopharyngeal swab samplesTime to RT-PCR virus negativity in nasopharyngeal swab samples

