### Eligibility criteria {10}

The population to be studied is adults (male or female), over 18 years old, hospitalized for COVID-19 infection confirmed by a positive RT-PCR of less than 10 days’ duration, associated with pneumonia and Sp02 ≥ 94% on oxygenotherapy. The patients will be recruited in the investigational sites declared on this study.

Women of childbearing potential (WOCBP) must use appropriate method(s) of contraception during the clinical trial (oral contraception, implant or intrauterine device (IUD). Pregnant women, women of childbearing potential (WOCBP) without effective contraception, women who are nursing, or patient under guardianship or trusteeship will not be included in the study. Furthermore, all sexually active male subjects must agree to use an adequate method of contraception throughout the study period and for 90 days after the last dose of study drug and agree to no sperm donation until the end of the study, or for 90 days after the last dose of XAV-19, whichever is longer.

The subjects cannot participate simultaneously in other interventional studies and until 3 months after the end of their participation to this study. All the inclusion and exclusion criteria are reported in Table 1.

**Table 1 Tab1:** Inclusion and exclusion criteria

Inclusion criteria	Exclusion criteria
❖ Male or female ≥18 years and ≤ 85 years	❖ Evidence of multiorgan failure (severe COVID-19)
❖ Women of childbearing potential (WOCBP) must use appropriate method(s) of contraception during the clinical trial (oral contraception, implant or IUD	❖ Mechanically ventilated (including ECMO)
❖ Willing and able to provide written informed consent prior to performing study procedures	❖ Receipt of immunoglobulins or any blood products in the past 30 days
❖ Hospitalized for COVID-19	❖ Psychiatric or cognitive illness or recreational drug/alcohol use that in the opinion of the investigator, would affect subject safety and/or compliance
❖ Positive SARS-CoV-2 RT-PCR in any body specimen (nasopharynx, saliva, sputum) ≤ 10 days before enrolment	❖ End-stage renal disease (eGFR < 15 ml/min/1,73 m^2^)
❖ Evidence of pulmonary involvement (on lung examination [rales/crackles] and/or chest-imaging [Chest X-ray or computed tomography])	❖ Child-Pugh C stage liver cirrhosis
❖ Requiring O2 supplement ≤6 L/min at screening	❖ Decompensated cardiac insufficiency
❖ Requiring O2 supplementation with SpO2 ≥ 94% on O2 therapy at screening	❖ **History of active drug abuse**

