### Sample size {14}

As it is a phase 2a, the number of patients was determined according to phase 2a’s relevant publications [23–25] . It was decided to enroll two cohorts of 8 patients (6 treated patients and 2 matching placebo in each cohort).

For the phase 2b, the predetermined sample size, controlling for the α risk of 5% and power of 80%, is 352 participants, based on an expected survival rate of patients giving up oxygen therapy at least at day 15 of 80% in the control group and 90% in the experimental group. In addition, the median duration of oxygen therapy in the control group is 8 days, and in the experimental group is 6 days. Hence the estimated hazard ratio is 0.75. The sample size was calculated following the formula of Schoenfeld [26] and the hazard ratio was estimated thanks to Cortes’ publication [27].

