## Statistical methods

### Statistical methods for primary and secondary outcomes {20a}

For the phase 2a study, the safety population included all subjects randomized into the study who received at least one dose of study drug. The intention-to-treat (exposed, ITT[E]) Population was defined as all subjects who met study criteria and were randomized into the study with documented evidence of having received at least one dose of randomized treatment and at least one post-baseline XAV-19 IgG SARS-CoV2 titer measurements. The Per-Protocol Population was defined as all subjects included in the ITTE Population excluding those who had at least one major protocol deviation.

The primary endpoint will be evaluated for ITTE Population by a Kruskal-Wallis test between all placebo patients and all treated patients.

Groups of treatment will be described according to variables in of the secondary endpoints. Categorical variables will be summarized by percent and continuous variable by means and standard error, and medians and interquartile range.

For the phase 2b, categorical variables will be summarized by percent and continuous variable by means and standard error, and medians and interquartile range. Survival rate and duration of oxygen therapy will be compared between the two groups for the primary endpoints.

For the secondary endpoint, quantitative endpoint will be compared using linear mixed model and qualitative data with logistic mixed model to take into account stratification factors. Time data’s will be analyzed using survival model. Fine and Gray method will be used to take into account competing risk.

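### NEWS2 is listed as two phase 2b outcomes with no day-1 covariate named; a single baseline-adjusted analysis would be a free improvement

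*Protocol article*

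**What the plan says.** Outcomes {12} of the Protocol article opens the phase 2b secondary endpoints with "National Early Warning Score (NEWS2) at day 15 and difference in NEWS2 between day 1" and day 15. Both the day-15 score and its difference from day 1 are thus outcomes. Objectives {7} describes the secondary objectives as comparisons between the two groups and also puts NEWS2 first.

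Statistical methods {20a} says "quantitative endpoint will be compared using linear mixed model and qualitative data with logistic mixed model to take into account stratification factors". No other term of the model is named. Sequence generation {16a} says only that randomization is balanced by blocks and names no strata.

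On virology, Outcomes {12} lists two nasopharyngeal measures for phase 2b, both under safety: viral load over day 1 to day 29, and time to RT-PCR negativity. Table 1 under Eligibility criteria {10} admits patients with "Positive SARS-CoV-2 RT-PCR in any body specimen (nasopharynx, saliva, sputum) ≤ 10 days before enrolment".

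**The concern.** If day-1 NEWS2 is not in the model, the first comparison ignores it and the second subtracts it in full. Neither is generally the best use of a baseline that has already been measured. The two estimated treatment effects then differ by exactly the chance difference between arms in mean day-1 NEWS2, so they can disagree, and the article does not say which one counts. At stake are the precision and clarity of the first-listed secondary efficacy endpoint.

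The virological concern is a mismatch of definitions. A patient can qualify on saliva or sputum, or on a nasopharyngeal swab several days old, and already be negative on the day-1 nasopharyngeal swab. Such a patient has nothing to clear in the specimen being measured. Including these patients dilutes any treatment contrast in time to negativity.

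**Working it through.** **Figures in the document.** The article gives no SD, correlation, effect size or power for NEWS2, so there is no NEWS2 figure to reproduce. The one sample size for phase 2b, 352, belongs to time to weaning from oxygen (Sample size {14}) and does not enter below.

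**Inputs.** Let r be the correlation between day-1 and day-15 NEWS2, and k the day-1 SD divided by the day-15 SD. Both are assumed: r at 0.2, 0.3 and 0.5; k at 1 and 0.5. The lower k allows for a narrower spread at entry, since every patient enters on oxygen at no more than 6 L/min with SpO2 of at least 94% (Table 1). The day-15 variance is set to 1.

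**Formula.** Subtracting b times the day-1 score from the day-15 score gives variance 1 + b²k² − 2bkr.
- Unadjusted day-15 score, b = 0: variance 1.
- Unadjusted change, b = 1: variance 1 + k² − 2rk, which is 2(1 − r) when k = 1.
- Day-1 score as covariate: in large samples b is estimated at its best value, r/k, and the variance is 1 − r², whatever k is.

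**Against the unadjusted day-15 score.** The adjusted variance is 0.96, 0.91 and 0.75 at r = 0.2, 0.3 and 0.5, a fall of 4%, 9% and 25%. In patients, the unadjusted score needs 1/0.96 = 1.04 to 1/0.75 = 1.33 times as many. As an illustration with 176 per arm, take an effect of 0.299 SD, which gives the unadjusted day-15 comparison 80% power at two-sided 5%. The adjusted analysis then has 82%, 84% and 90% power.

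**Against the unadjusted change.**

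| k | r | best weight r/k | change variance | adjusted variance | ratio |
|---|---|---|---|---|---|
| 1 | 0.2 | 0.2 | 1.60 | 0.96 | 1.67 |
| 1 | 0.3 | 0.3 | 1.40 | 0.91 | 1.54 |
| 1 | 0.5 | 0.5 | 1.00 | 0.75 | 1.33 |
| 0.5 | 0.2 | 0.4 | 1.05 | 0.96 | 1.09 |
| 0.5 | 0.3 | 0.6 | 0.95 | 0.91 | 1.04 |
| 0.5 | 0.5 | 1.0 | 0.75 | 0.75 | 1.00 |

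The change score therefore needs 33% to 67% more patients when the SDs are equal, and about 0% to 9% more when the day-1 SD is half the day-15 SD. In the last row the best weight is already 1, so the change score loses nothing.

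**Why one analysis is enough.** Write day 15 = a + τ·arm + β·day 1 + error. Subtracting day 1 from both sides gives change = a + τ·arm + (β − 1)·day 1 + error. The treatment effect τ is the same, so once day 1 is a covariate the two listed outcomes give a single estimate.

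**Time to negativity.** Eligibility refers to several specimen types within 10 days before enrolment. The endpoint refers to nasopharyngeal swabs from day 1. The article states no requirement for a positive nasopharyngeal swab on day 1, and gives no figure for how many patients would lack one, so the dilution cannot be sized.

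**The case against.** The strongest reply is that an endpoint list is not an analysis. The article commits to a linear mixed model and gives stratification factors as a reason for it, not as a closed list of covariates. A condensed article may leave the full list to an analysis plan. A change score can itself be analysed with day 1 as a covariate, so listing both outcomes does not commit the sponsor to an inefficient method. All of this stands, and it is why the point is a recommendation.

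Several stronger readings are tempting, and the documents do not support them.
- A reader might infer that NEWS2 will be compared raw, with day 1 left out. No section says so.
- A reader might extend the point to viral load. Outcomes {12} defines viral load over day 1 to day 29, not as a day-15 value or a change, and a repeated-measures model can use day 1 as a response or a covariate.
- A reader might quote the 33% to 67% penalty alone. It assumes equal SDs, which conflicts with arguing that entry criteria narrow the day-1 score. How far they narrow it is itself unknown: NEWS2 also scores respiration rate, blood pressure, pulse, consciousness and temperature, which the oxygen criteria do not directly restrict.
- A reader might infer that a patient negative on day 1 counts as an immediate event. No such rule is stated. The time for such a patient is simply undefined in the article.

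What survives the reply is that two outcomes are listed for one score, the baseline is not named, and naming it costs nothing.

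**Conclusion.** The point holds as a free improvement, not as an error in the plan. As worded, the article allows two NEWS2 results that can disagree, each in large samples no more precise than one baseline-adjusted estimate and usually less.

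With r assumed between 0.2 and 0.5, adjustment cuts variance by 4% to 25% relative to the unadjusted day-15 score. That range does not depend on the SD ratio. The gain over the change score does: about 0% to 9% in patients at a ratio of 0.5, and 33% to 67% at a ratio of 1. The documents supply neither r nor the ratio, so the size in this trial remains unknown. The formulas are large-sample results with a common correlation and SDs in both arms.

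The time-to-negativity point is secondary. The two definitions do not match, but the effect cannot be quantified. The sample size of 352 and the primary endpoint are untouched.

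**What to change.** - Specify one NEWS2 analysis: day-15 NEWS2 in the linear mixed model with day-1 NEWS2, taken before the first infusion, as a covariate alongside any stratification factors. Report the adjusted mean difference with its confidence interval. The change from day 1 can still be described by arm but needs no separate test.
- Define the analysis set for time to RT-PCR negativity as patients with a positive nasopharyngeal swab on day 1. If that swab precedes the first infusion, the restriction uses a baseline fact and keeps the randomized comparison within that set.
- If the analysis plan already does either of these, no change is needed beyond aligning the wording.

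The cost is wording only. The day-1 NEWS2 is already needed for the listed difference, and nasopharyngeal sampling already starts on day 1. No extra patients, visits or samples are required.
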